### 2.6. Intervention

#### 2.6.1. Health Education Programme G0 (Control Group)

Participants assigned to the control group (G0) will receive a standardized informational leaflet focused on evidence-based lifestyle modifications. This material will outline comprehensive instructions and recommendations for maintaining an active lifestyle, promoting self-care, and fostering healthy habits.

The content will be aligned with World Health Organization recommendations on risk reduction in cognitive decline and dementia [29]. The key areas covered in the intervention include:Nutritional optimization: Adoption of a balanced and nutritious diet.Physical & Mental Activity: Regular exercise and engagement in cognitively stimulating tasks.Psychosocial Factors: Maintenance of robust social connections and effective stress management techniques.Sleep Hygiene: Strategies for ensuring restorative and adequate sleep.Metabolic & Toxic Habits: Proper hydration, smoking cessation, and the avoidance of excessive alcohol consumption.

Strictly following the study design, this group will not receive cognitive individual or group stimulation. This group serves as a baseline comparison to evaluate the natural progression of cognitive symptoms under standard care and general health recommendations.

To capture the true, unaltered natural progression of neurocognitive symptoms under standard oncological care, the G0 group follows a passive, no-contact design between evaluations. While this limits real-time behavioral tracking, it deliberately prevents the introduction of reactive biases or artificial behavioral modifications often triggered by frequent researcher contact (the Hawthorne effect). Nonetheless, any spontaneous or clinically significant changes in participants’ lifestyle, sleep hygiene, or psychological status during this period will be captured and quantified via the multi-domain secondary psychometric outcomes (such as the PSQI and Hamilton scales) administered during the post-intervention assessment (T1).

#### 2.6.2. Cognitive Training Group (CT) G1

Participants in the Cognitive Training (CT) group (G1) will undergo a structured programme focused on everyday cognition, administered individually to each patient. The intervention will be delivered through a meticulously developed dossier designed specifically for the objectives of this study. Notably, all participants in this arm will receive identical tasks, with no individualized adaptations for difficulty level or functional profile.

The intervention is structured into four consecutive one-month training periods (P1–P4), totaling 80 activities (20 activities per period). Participants are required to complete five activities per week. To monitor treatment adherence and ensure compliance with therapeutic guidelines, a dual follow-up system will be implemented:Remote Follow-up: Conducted via video call at the conclusion of P1 and P3 (Months 1 and 3).In-person Follow-up: Conducted at the clinic at the conclusion of P2 and P4 (Months 2 and 4) to evaluate progress and address emergent concerns.

The final evaluation for G1 will coincide with the completion of the fourth training period (P4). This group serves to control the effects of cognitive stimulation and professional monitoring without the specific multimodal components of the ALMA.

#### 2.6.3. ALMA Group Intervention G2

The ALMA intervention is designed as a cognitive intervention programme tailored specifically for breast cancer patients. The primary objective is to address the effects of commonly known chemobrain by targeting cognitive domains commonly affected in CRCI. Beyond cognitive recovery, the programme aims to support self-esteem and patient empowerment through personalized and ecologically valid activities.

The intervention will be delivered through face-to-face group sessions at the Faculty of Psychology of the University of Salamanca. Each ALMA group will include up to six participants. If more than six participants are allocated to G2, additional groups will be created and delivered using the same intervention manual, session structure, materials, and monitoring procedures.

Group size will be limited to six participants to facilitate interaction, individualized support, and consistency in intervention delivery. The programme will span four months, with two 120 min sessions per week, resulting in a total of 32 sessions. The ALMA intervention is characterized by the following components:Targeted Cognitive Stimulation: Structured exercises focusing on memory, executive functions, attention, language, and mathematical/logical reasoning with dynamic adjustments to address specific patient deficiencies.Neuro-education & Health Literacy: Integrative discussions on neuroscience, cognitive health, and overall well-being to foster self-management.Group Dynamics: A collaborative environment designed to facilitate social support and emotional resilience among peers.

The activities will be adaptively tailored to the participants’ functional profiles, ensuring that the stimulation is both accessible and clinically relevant.

To ensure the replicability of the ALMA intervention, the operational components, session structure, materials, and monitoring procedures will be standardized and described in detail in Supplementary Material S1.

Each session will last 120 min and will follow a structured format consisting of welcome and psychoeducation, cognitive intervention, and review and wrap-up. Each session will follow a structured schedule to support consistency:Welcome and Psychoeducation (25 min): The session will commence with a “check-in” to assess the well-being of all participants. Subsequently, the group will engage in a discussion of neuropsychological topics with a particular focus on the phenomenon known as “chemobrain.”Cognitive Intervention (70 min): Participants will engage in cognitive exercises encompassing the domains of memory, attention, language, executive functions, and mathematical/logical reasoning.Review and Wrap-Up (25 min): A thorough explanation and comprehensive review of the completed activities will be provided, along with the group’s feedback.

In terms of the progression of difficulty and the roadmap, the intervention will not be static but will follow a curricular progression.

The exercises will be adapted to the patients’ particular impairments and functional profiles, with the activities structured primarily based on their subjective complaints, prioritizing the domains with the most significant perceived deficits.

The principal investigator will prepare the worksheets containing the cognitive stimulation activities for each session, as well as the psychoeducation topics. The materials to be used in the intervention consist of cognitive stimulation activity worksheets, writing implements, erasers, colored pencils, audio equipment, and the previously referenced games. The implementation of particular materials, including cognitive stimulation activities and games, will help ensure that all participants receive equivalent stimulation, notwithstanding the formation of additional replication groups in the future.

Mechanisms will be established to ensure the consistency and rigor of this study. Consequently, the intervention will adhere to the predetermined clinical framework for Group G2. Furthermore, adherence will be documented through systematic monitoring of attendance using a follow-up log with standardized codes for absences. A success threshold will be applied, requiring a minimum attendance rate of 70% (22 out of 32 sessions) to validate the intervention. Furthermore, a meticulous record of the reasons for withdrawal will be maintained to assess the feasibility of the protocol.

To guarantee the fidelity of the intervention and its replicability in future groups, a manual describing the ALMA Protocol will be created. This manual will be based on a guide developed by the researcher. The guide will outline the objectives, content, and duration of each of the 32 sessions. This manual is designed to ensure that the approach to neuroeducation, cognitive intervention, and group dynamics remains consistent throughout the 4-month period. The progression of the activities will be documented, and the activities will be adapted according to the patients’ functional profiles. This approach is designed to ensure that the stimulation is both effective and primarily focuses on the most affected cognitive functions.

The investigator who is responsible for the interventions will be a professional who has obtained the qualifications necessary for the task.

The organizational structure and the specific components of each study arm are summarized in Figure 1. This figure provides a comprehensive overview of the three-group design, highlighting the ALMA protocol as the core clinical framework. It details the internal structure of the G2 sessions comprising psychoeducation, tailored cognitive intervention, and group feedback as well as the longitudinal progression of the four-month intervention roadmap.

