## 2. Materials and Methods

### 2.1. Study Design and Setting

This prospective, longitudinal, randomized controlled trial aims to evaluate the efficacy of the ALMA cognitive intervention programme in addressing cancer-related cognitive impairment. The effects of ALMA will be compared with an individual cognitive training programme and a health education control group.

The trial design has been developed in accordance with the Standard Protocol Items: Recommendations for Interventional Trials (SPIRIT) 2013 guidelines [26]. This one-year clinical investigation will be conducted at the University of Salamanca (Spain), specifically within the Department of Medical Oncology at the University Healthcare Complex of Salamanca.

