### 2.2. Participants and Eligibility Criteria

Recruitment will be initiated by a qualified oncologist at the University Healthcare Complex of Salamanca, who will identify potential candidates and provide preliminary information regarding the trial. If interested, patients will be scheduled for an in-person consultation with a member of the research team. During this session, the study’s objectives and procedures will be detailed, and any participant question will be addressed.

To determine final eligibility, screening assessment will be conducted. This process will include a baseline research protocol, including a battery of neuropsychological assessments and standardized questionnaires designed to evaluate sleep quality, anxiety symptomatology. Furthermore, written informed consent will be obtained from all subjects prior to any study-related procedures, in accordance with the Declaration of Helsinki.

A summary of the Initial Assessment Protocol and Anamnesis Phase is provided in Table 1. Potentially eligible participants will be identified consecutively and randomized after consent and baseline assessment.

Women aged 18 years and over who have been diagnosed with histologically confirmed breast cancer, at stages I–IV, and who are receiving active oncological treatment at the time of recruitment are eligible to participate. Active treatment will include chemotherapy, radiotherapy, and hormone therapy. Patients with metastatic disease will be included in the study. The time since diagnosis, disease stage, recurrence status, metastatic status, and treatment modality will be recorded as clinical variables rather than used as restrictive eligibility criteria. The specific inclusion and exclusion criteria are described in Table 2 and detailed below:

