### 2.3. Recruitment

Participants will be recruited from the Department of Medical Oncology at the University Healthcare Complex of Salamanca. Consecutive identification of potentially eligible women by the oncology team during routine clinical care is to be conducted in accordance with the predefined inclusion and exclusion criteria. Patients who appear to meet the initial eligibility criteria will receive preliminary verbal information about the study. If they express interest, they will be referred to a member of the research team for a detailed explanation of the trial procedures.

The estimated recruitment period will be 12 months, or until the target sample size of 63 participants has been reached. A screening log will be maintained to document the number of patients assessed for eligibility, excluded before randomization, reasons for exclusion when available, number of patients who decline participation, and number of participants randomized to each study arm.

In the event that the intended sample size is not attained within the anticipated recruitment period, the research team may opt to extend the recruitment period, enhance coordination with the oncology service, augment the frequency of screening of outpatient clinic schedules, and provide additional information sessions to eligible patients. Any substantial change in the recruitment strategy, recruitment period, or study setting will be submitted to the Research Ethics Committee for approval when required and will be updated in the trial registry where applicable.

Refusal to participate or withdrawal from the study will not affect participants’ usual oncological care or their relationship with the clinical team.

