### 2.5. Randomization and Allocation Concealment

To ensure numerical balance and a homogeneous distribution of prognostic factors across the three study arms, a stratified block randomization method will be employed. Randomization will be stratified based on two baseline prognostic variables: (1) baseline cognitive status, categorized according to the Montreal Cognitive Assessment score (MoCA < 26 vs. ≥26), and (2) oncological treatment modality, classified according to its systemic neurotoxic potential: systemic chemotherapy with or without radiotherapy versus endocrine/hormone therapy or localized radiotherapy alone.

Following stratification, participants will be randomly assigned to one of the three study arms using randomly varied blocks of size 3 and 6. The random allocation sequence will be generated before the start of recruitment by an independent researcher using Epidat 4.2 software. This researcher will not be involved in participant recruitment, eligibility assessment, baseline or post-intervention outcome assessment, intervention delivery, data management, or statistical analysis.

The random allocation sequence will be stored in a password-protected file and will remain inaccessible to the Principal Investigator, oncology team, intervention providers, outcome assessors, and statistician until eligibility has been confirmed, written informed consent has been obtained, and all baseline assessment procedures (T0) have been completed.

After completion of T0, the Principal Investigator will access the next available allocation within the corresponding stratified stratum and assign the participant to the allocated study arm. The assigned group will then be communicated to the intervention coordinator. The allocation will be recorded in a secure allocation log maintained separately from the assessment database.

This procedure will ensure that group allocation cannot influence eligibility confirmation, informed consent, or baseline assessment. Because the Principal Investigator will become aware of group allocation after T0, this trial will be conducted as an open-label study, and this limitation will be addressed through standardized assessment procedures and blinded statistical analysis using neutral group labels.

The three study arms are defined as follows:G0 (Control Group): Health Education Programme.G1 (Active Comparison): Cognitive Training (CT).G2 (Experimental Group): ALMA.

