### 3.6. Participant Evaluation

The evaluation of participants will occur at two distinct time points:

Baseline Evaluation (T0): Conducted immediately after recruitment and prior to randomization. This stage ensures the documentation of all sociodemographic and clinical variables, alongside the administration of objective cognitive tests, without the influence of group assignment.

Post-Intervention Evaluation (T1): Scheduled upon the culmination of the four-month intervention period for all groups.

Following the baseline evaluation, participants will undergo randomization to their assigned intervention arm (ALMA, Cognitive Training, or Health Education).

For a comprehensive overview of the pertinent data, please refer to the table provided in Supplementary Material S2. Table follows the SPIRIT participant timeline structure and reflects the protocol schedule described in the manuscript.

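### Individual randomisation, group delivery of ALMA and a T1 tied to the end of the intervention may make T0–T1 longer in G2 than in the other arms

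*Protocol article*

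**What the plan says.** **Enrolment.** Section 2.2 of the Protocol article: "Potentially eligible participants will be identified consecutively and randomized after consent and baseline assessment". Section 2.5 allocates woman by woman: after T0, "the Principal Investigator will access the next available allocation within the corresponding stratified stratum and assign the participant to the allocated study arm". Section 3.6 places T0 directly after recruitment and before randomisation.

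**Delivery.** G0 receives a leaflet and then has no contact until T1 (Section 2.6.1). G1 receives an individual dossier covering four one-month periods (Section 2.6.2). G2 is delivered face to face in groups: "Each ALMA group will include up to six participants. If more than six participants are allocated to G2, additional groups will be created" (Section 2.6.3). That programme has 32 sessions over four months, "the intervention will not be static but will follow a curricular progression", and a guide sets out the content of each session.

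**T1.** Section 3.6 has it "Scheduled upon the culmination of the four-month intervention period for all groups". For G1, Section 2.6.2 places it at the end of the fourth period.

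**Endpoint and model.** The primary endpoint is the between-group difference in MoCA change, T1 minus T0 (Sections 3.1 and 3.2). The model in Section 3.9 has fixed effects for group, time and their interaction, and a random intercept. It describes no term for elapsed time.

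**Calendar.** Section 2.3: "The estimated recruitment period will be 12 months, or until the target sample size of 63 participants has been reached". Section 2.1 calls the trial a one-year investigation.

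**The concern.** A leaflet or an individual dossier has no reason to wait. A group programme cannot begin with the first woman allocated to it. Because T0 comes before randomisation and T1 follows the end of the intervention, any time spent waiting for a group adds directly to the T0–T1 interval, and only in G2.

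The primary endpoint is a difference in change scores, and G0 is there to show the natural course over the study interval (Section 2.6.1). If G2 is observed for longer, its change includes extra weeks of treatment effects, recovery or decline that G0 and G1 do not have. The model treats T0 and T1 as two occasions, so it would assign that difference to the Group × Time term. Randomisation gives no protection, because the delay arises after allocation and depends on the arm.

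**Working it through.** The article states no waiting time and no T0–T1 interval, so there is no figure of its own to reproduce. The check is accrual arithmetic on its own inputs.

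**Inputs.** 63 women and 21 per arm (Section 2.4); 12 months of recruitment (Section 2.3); at most six per ALMA group, no minimum stated, four-month programme (Section 2.6.3).

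**G2 accrual.** r = 21/12 = 1.75 women per month.

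**Wait, with even accrual and a group of k starting when its last member is allocated.** The first woman waits (k − 1)/r, the last waits 0, and the mean is (k − 1)/(2r).

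| Group starts at | First woman waits | Mean wait in the group |
|---|---|---|
| 3 | 2/1.75 = 1.14 months | 0.57 |
| 4 | 3/1.75 = 1.71 months | 0.86 |
| 5 | 4/1.75 = 2.29 months | 1.14 |
| 6 | 5/1.75 = 2.86 months | 1.43 |

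Twenty-one women make groups of 6, 6, 6 and 3. The mean over the arm is then (18 × 1.43 + 3 × 0.57)/21 = 1.31 months.

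**Resulting interval.** With groups started at six, T0–T1 in G2 runs from 4.0 to 4 + 2.86 = 6.9 months. It is about 4 months in G0 and G1 if they start soon after allocation.

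**Sensitivity to pace.** For groups of six, the first woman waits 5/(21/8) = 1.90 months if recruitment takes 8 months, and 5/(21/18) = 4.29 months if it takes 18.

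**Irregular accrual.** A simulation used 63 uniformly distributed arrivals over 12 months, four equally likely strata and permuted blocks of 3 and 6. Groups started when full, and a last partial group started at its last entrant.

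| Group starts at | Mean wait | Share waiting over 1 month | Longest wait per trial, on average |
|---|---|---|---|
| 6 | 1.27 months | 52% | 3.6 months |
| 3 | 0.53 months | 21% | 2.1 months |

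**What this could do to the contrast.** Bias ≈ monthly MoCA drift × mean excess interval. The documents give no drift. Purely as an assumption, take 0.2 to 0.5 points per month in either direction:

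- Groups of six: 0.2 × 1.31 = 0.26 to 0.5 × 1.31 = 0.65 points, which is 9% to 22% of the planned 2.95.
- Groups of three: 0.2 × 0.57 = 0.11 to 0.5 × 0.57 = 0.29 points.

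**Calendar.** 12 + 4 = 16 months before any group wait, against the one year of Section 2.1.

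**The case against.** **The mechanism is partly inferred.** The article does not say that groups are closed, that a group must be full before it starts, or that G0 and G1 start at once. The stated size is a maximum, so smaller groups and shorter waits are allowed, and rolling entry is not excluded. This stands, and it is why the point is conditional. Even so, a session-by-session guide and a curricular progression fit rolling entry poorly, and starting at three shortens the wait without removing it.

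**The supplements may settle it.** Supplementary Materials S1 and S2 and Figure 1 are not shown and may contain start rules. That cannot be excluded. However, Section 3.6 says the S2 table reflects the schedule described in the manuscript, and the T1 anchor is stated in the article itself.

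**Stronger readings that the documents do not support:**

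- *All G2 women wait about three months.* Only the first woman in a full group of six does so under even accrual; the sixth does not wait. Nor is three months a ceiling if accrual is irregular or slow.
- *Women whose treatment ends, or who drop out, while waiting are lost from G2 alone.* Section 2.2 requires active treatment at recruitment, and nothing removes a woman when it ends. Section 2.9 encourages final assessments after discontinuation, and Section 3.9 keeps all randomised women in their arm. Extra dropout during a wait is possible but speculative. A later treatment change also does not invalidate a baseline stratum.
- *The contrast is biased by a known amount or in a known direction.* The drift above is assumed.
- *Only 63 × 8/12 = 42 women could reach T1 within one year.* Section 2.3 calls the recruitment period estimated and allows it to be extended, and nothing says that follow-up stops at one year. The mismatch is one of wording.

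**Conclusion.** The point holds in conditional form. Individual T0 and randomisation, group delivery and a T1 tied to the end of the intervention together mean that any wait for a group lengthens T0–T1 in G2. Nothing in the visible article equalises the interval across arms.

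The excess averages about 1.3 months if groups start at six and about 0.6 if they start at three. This assumes 12 months of even accrual, a common start within each group, and G0 and G1 starting soon after allocation. The effect on the MoCA contrast is unknown in size and sign. It deserves correction before enrolment, because unequal intervals cannot be undone afterwards. The one-year duration is a separate, plain inconsistency with Sections 2.3 and 2.6.3.

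**What to change.** 1. **Common start (Sections 2.6.1 to 2.6.3).** Give all women randomised in the same accrual period one start date. Issue the G0 leaflet and the G1 dossier when that period's ALMA group starts. Preferably define the periods by calendar dates, so that their end does not depend on G2 filling up.
2. **Common T1 window (Section 3.6).** Count T1 from that start date, with the same window in all arms. Any wait between T0 and start then falls on all arms alike.
3. **T0 close to start, where feasible.** Schedule T0 and randomisation near the planned group start.
4. **Reporting and analysis (Section 3.9).** Report the T0–T1 interval by arm and add a sensitivity analysis using elapsed time. This cannot replace items 1 and 2. If only G2 varies in interval, the effect of elapsed time would be estimated almost entirely within G2.
5. **Duration (Section 2.1).** Replace one year with at least 16 months.

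**Cost.** Items 1 and 2 need wording and scheduling. Some G0 and G1 women start later, and the calendar lengthens slightly. Shorter accrual periods reduce the wait but give smaller groups: two months yields about 2 × 1.75 = 3.5 G2 women.

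Enrolling entirely in cohorts would be heavier. At 63/12 = 5.25 women per month, gathering 18 (six per arm) takes 18/5.25 = 3.4 months. Their T0 batteries, with the PECC alone at 35 minutes, would then fall together on the one researcher who assesses and also delivers ALMA. Item 3 is therefore limited to what is feasible.

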### 2.8. Participant Enrollment, Withdrawal and Adherence

Adherence to the enrollment and withdrawal guidelines will be checked by systematically recording attendance at all group sessions. A minimum threshold of 70% attendance (22 out of 32 sessions) has been established to consider the intervention complete. To maximize retention and mitigate non-attendance, the following strategies will be implemented:Automated Reminders: Notifications will be sent via WhatsApp 24 h prior to each session.Scheduling Flexibility: Session hours will be adapted to accommodate participants’ clinical and personal schedules.Group Cohesion: The intervention’s group nature is expected to foster social support, reducing the likelihood of dropout.

All absences will be documented in a systematic monitoring log using a binary system (presence/absence) and standardized coding for causes (e.g., clinical discomfort, logistical barriers, or personal reasons). While absences due to medical causes (appointments or post-treatment side effects) will be recorded for qualitative analysis, they will still be included in the final calculation of the 70% adherence threshold.

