### 3.9. Statistical Analysis

All analyses will be conducted according to the intention-to-treat (ITT) principle, including all randomized participants in the groups to which they were originally allocated, regardless of adherence to the intervention, thereby ensuring that the primary effectiveness analysis remains fully powered even if a significant proportion of participants fail to meet compliance thresholds. A secondary per-protocol analysis may be conducted including participants who complete the post-intervention assessment and, in the intervention arms, meet the predefined adherence criteria (≥70% attendance). In the event that a large majority of participants fail to reach this updated 70% attendance threshold due to severe treatment-related toxicity, a secondary sensitivity dose–response analysis will be implemented, modeling session attendance as a continuous covariate to evaluate the threshold-independent impact of intervention volume on neurocognitive outcomes.

Descriptive statistics will be used to summarize baseline sociodemographic and clinical characteristics by study arm. Continuous variables will be presented as means and standard deviations or medians and interquartile ranges, depending on their distribution. Categorical variables will be presented as frequencies and percentages. Baseline comparability between groups will be described, but statistical testing of baseline differences will not be used to determine participant inclusion or exclusion from the analysis.

The primary effectiveness analysis will evaluate change in Montreal Cognitive Assessment (MoCA) total score from baseline (T0) to post-intervention assessment (T1). Linear mixed models (LMM) will be constructed using a Restricted Maximum Likelihood (REML) estimation approach. The model will include fixed effects for group, time, and the Group × Time interaction term, and a parsimonious random-effects structure restricted to a random intercept for each participant to account for within-subject correlation across time while excluding random slopes. The Group × Time interaction will be the main parameter of interest. Both unadjusted and adjusted models will be calculated to verify the robustness of the intervention effect.

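### The adherence threshold does not match its own count (22 of 32 sessions is 68.75%, not 70%), is not defined in G1's units, and its attendance-based fallback should not be read causally

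*Protocol article*

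**What the plan says.** Section 2.6.3 describes ALMA as a four-month programme "with two 120 min sessions per week, resulting in a total of 32 sessions". It then sets a success threshold "requiring a minimum attendance rate of 70% (22 out of 32 sessions) to validate the intervention". Section 2.8 restates it: "A minimum threshold of 70% attendance (22 out of 32 sessions) has been established to consider the intervention complete". The same section bases the check on "systematically recording attendance at all group sessions" and says of absences for medical causes that "they will still be included in the final calculation of the 70% adherence threshold".

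Section 3.9 makes intention-to-treat the primary analysis. It allows an optional per-protocol analysis of women who complete the post-intervention assessment and, "in the intervention arms, meet the predefined adherence criteria (≥70% attendance"). No session count is given there. If a large majority miss the threshold because of severe treatment-related toxicity, a secondary sensitivity analysis follows, "modeling session attendance as a continuous covariate to evaluate the threshold-independent impact of intervention volume on neurocognitive outcomes".

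G1 has no group sessions. Section 2.6.2 gives it an individual dossier "totaling 80 activities (20 activities per period"), with two video and two in-person follow-up contacts.

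**The concern.** Three things in the adherence rule do not fit together.

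- **Percentage against count.** The threshold is printed both as a percentage and as a number of sessions, and the two disagree. Membership of the per-protocol set would depend on which one the analyst programs.
- **G1.** The percentage is worded as attendance and applied to both intervention arms, but the only attendance that the protocol records is at G2 group sessions. G2 versus G1 is one of the two planned comparisons on the primary outcome. A per-protocol version of it would need a G1 rule that the text does not give.
- **The fallback.** The dose–response model is used when toxicity is held responsible for low attendance, and its slope is to be read as an effect of intervention volume. The Introduction lists treatment-related neurotoxicity and fatigue among the contributors to cognitive impairment. The same factor may therefore drive both attendance and outcome.

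At stake are the per-protocol result, the label of a completed intervention, and the interpretation of one contingent sensitivity analysis. It is better to settle these before data exist. According to Section 2.11 and the Limitations, the person who delivers ALMA also records attendance and assesses outcomes.

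**Working it through.** **1. Percentage against count**

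Inputs: 32 sessions, and a minimum of 70% printed as 22 of 32 (Sections 2.6.3 and 2.8); ≥70% (Section 3.9).

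- 0.70 × 32 = 22.4. Rounding to the nearest whole session, or down, reproduces the printed 22.
- 22/32 = 0.6875, which is below 0.70.
- 23/32 = 0.71875, the smallest count that meets ≥70%.
- The gap is one session, 1/32 = 3.1 percentage points.

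Could the denominator shrink? If one medical absence were excused, 22/31 = 0.710 would meet 70%. The natural reading of Section 2.8 rules this out, because medical absences stay in the calculation and the denominator remains 32.

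How many women could fall at exactly 22? The documents give no attendance distribution. As an assumption, take independent attendance with the same probability p at each of the 32 sessions, and 21 women in G2 (Section 2.4):

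| p | P(exactly 22) | Expected of 21 | P(≥22) | P(≥23) |
|---|---|---|---|---|
| 0.60 | 0.089 | 1.9 | 0.205 | 0.116 |
| 0.65 | 0.136 | 2.9 | 0.405 | 0.268 |
| 0.70 | 0.149 | 3.1 | 0.644 | 0.495 |
| 0.75 | 0.110 | 2.3 | 0.846 | 0.737 |
| 0.80 | 0.049 | 1.0 | 0.959 | 0.910 |

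That is about 1 to 3 women, each 1/21 = 4.8% of the arm. Real attendance will vary more between women than this model allows, so the table shows only that the boundary case is realistic.

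**2. The rule in G1**

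Inputs: five activities a week, 80 in total, and four follow-up contacts (Section 2.6.2).

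- In activities: 0.70 × 80 = 56.
- In contacts: 0.70 × 4 = 2.8, so 3 of 4 (75%), since 2 of 4 is 50%.

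These select women on different grounds, and the protocol chooses neither.

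**3. The fallback model**

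Suppose that sessions have no effect at all, and that toxicity correlates −a with attendance and −b with MoCA change. Attendance and change then correlate a × b through toxicity alone. The documents give neither a nor b, so both are assumed. Rejection rates come from 20,000 simulated samples of 21 women for each pair, using an unadjusted two-sided 5% test:

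| a | b | Induced correlation | Rejection rate |
|---|---|---|---|
| 0.3 | 0.3 | 0.09 | 6.4% |
| 0.3 | 0.5 | 0.15 | 10.1% |
| 0.5 | 0.3 | 0.15 | 9.6% |
| 0.5 | 0.5 | 0.25 | 19.8% |
| 0.7 | 0.3 | 0.21 | 15.2% |
| 0.7 | 0.5 | 0.35 | 34.6% |

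Under weak links the error is close to nominal; under strong links it is large. This shows that confounding is possible, not that it will occur.

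**The case against.** **Reach.** A reader might infer that the trial's main result is compromised. It is not. The primary analysis includes every randomized woman regardless of adherence, the per-protocol analysis is optional, and the fallback needs a large majority to miss the threshold. This limit stands.

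**A rounding slip.** The count of 22 is the same in both sections that define the threshold, and Section 3.9 refers back to criteria already defined, so an analyst might simply use 22. That is a plausible guess at the intent. It still conflicts with a stated minimum and with the ≥ sign.

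**G1.** A reader might infer that the rule cannot be applied to G1. That goes too far. G1 has a countable dose, and its contacts are meant to monitor adherence. An article may also leave the exact per-protocol definition to a fuller document. What stands is narrower: the criterion as worded does not fit G1.

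**The fallback.** A reader might infer that the attendance slope would favour ALMA even if ALMA did nothing. The documents do not support this. No document gives the size of any effect of toxicity on MoCA change, and the rejection rates above rest on assumed correlations. A slope within G2 is also not a contrast between arms. Section 3.9 does not state the model's covariates, and it leaves treatment modality, stage and performance status open for sensitivity analyses, so some adjustment is not excluded.

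**A stronger remedy.** Replacing the model with a complier-average effect at a session cut-off is tempting. It would require that attendance below the cut-off has no effect, which is doubtful for a woman who attends 20 sessions. Relabelling is enough.

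**Conclusion.** The point holds in limited form. The contradiction between 70% and 22 of 32 is plain arithmetic and needs no assumption. It amounts to one session, and to perhaps 1 to 3 of 21 women under the binomial assumption. The criterion is undefined for G1 as worded, though easily defined. The fallback could be confounded under the very condition that triggers it; the direction and size of any bias cannot be established from the documents. The consequences are confined to the optional per-protocol analysis, the contingent sensitivity analysis and the label of a completed intervention. The change is worth making because a decision threshold is printed inconsistently and correcting it costs almost nothing. No view is taken on which attendance level is clinically adequate.

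**What to change.** 1. Reconcile the percentage and the count to a single value, and print it identically in Sections 2.6.3, 2.8 and 3.9. Giving the number of sessions in Section 3.9 would remove the ambiguity.
2. State the G1 per-protocol criterion in G1's own units, fixed before data are seen. A proportion of the 80 activities is one example (70% would be 56).
3. Label the attendance model descriptive and non-causal, and drop the claim that it evaluates the impact of intervention volume.

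The cost is a few wording changes and a tally of completed G1 activities at the four planned contacts. Section 2.6.2 says that these contacts monitor adherence but does not say that activities are counted, so the tally is a small addition. The sample size, the primary model and the assessment schedule do not change.
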